### Implementation

A CRC will generate the allocation sequence, enroll participants, and assign participants to interventions.

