### Participant recruitment

Participants will be recruited at three hospitals in the Republic of Korea, DongShin University Gwangju Oriental Hospital, DongShin University Mokpo Oriental Hospital, and KyungHee Korean Medicine Hospital. The study will be publicized via local newspapers, the Internet, and posters in communities and hospitals. Participants will be given an explanation of the study by the Clinical Research Coordinator (CRC), and will voluntarily sign a form consenting to participation. The CRC will continuously monitor the medical conditions of enrolled participants to maximize adherence to intervention protocols.

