### Randomization

After written informed consent and baseline measurements are obtained, SPSS version 22.0 (IBM Corporation, Armonk, NY, USA) will be used to assign a serial number to the 60 research volunteers and to randomly allocate 30 of them into each group. The serial number codes will be inserted into opaque envelopes that will be sealed and kept in a double-locked cabinet, and opened in the presence of the patient and a guardian.

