### Blinding

During the course of this clinical trial, the assessor will not come into contact with any of the participants except at the time of assessment. Furthermore, under no circumstances will unblinding be permitted. To prevent risks of bias with regard to selection, performance, and attrition caused by non-blinding of participants and practitioners, only individuals without conflicts of interest or preconceived positions will be involved in this study. All practitioners will receive training in clinical trials before participation in this study.

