### Confidentiality and data management

Participants’ identification records will be kept confidential until the results of the study are published. All documents related to the trial, including CRFs, will be recorded and labeled with participant identification codes and will not show the name of the participant. The serial number codes will be stored in sealed, opaque envelopes, kept in a double-locked cabinet, and opened in the presence of the patient and a guardian. All participant data will be recorded in Excel files by the CRC. Additionally, raw data (CRFs) will be stored in a cabinet until the end of the study. Written informed consent for the publication of their individual details and accompanying images will be obtained from the participants.

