## Discussion

Nearly all ankle sprains are simple grade-I (mechanically stable) or grade-II (some joint laxity) ligament sprains. Grade-III sprains (clinical and/or radiological evidence of instability) constitute a small minority [8]. Although the prevalence of grade-III sprains is low, there is strong evidence supporting the use of immobilization and, occasionally, surgical correction in the management of these injuries [31]. Conversely, clinical standards for the acute management of grade-I and -II ankle sprains are not well defined and there is no evidence supporting a clinically important improvement in outcome with the addition of supervised physiotherapy to usual care in grade-I and -II ankle sprains [32]. KT is one of the functional treatment options for ankle sprain in TKM, which include tape, a semi-rigid brace, and a lace-up brace. “Meridian muscle” is a TKM concept that includes the muscles, ligaments, and tendons of the part where 12 meridians pass. Ankle meridian tendino-musculature and the figure-of-eight shape form of KT treatment is a KT technique applied to the ankle and surrounding meridian muscle, including from ST42 to ST36 over the tibialis anterior muscle to assist active dorsiflexion and inversion, and from GB42 to GB34 over the peroneus longus and brevis muscles to assist active ankle eversion [22].

The objective of the proposed study is to investigate the potentially synergistic effects of KT combined with acupuncture in grade-I and -II ankle sprains, but notably, the study has some limitations. First, there is concern that the short treatment period planned to minimize dropout rates may affect the results of the study. Second, we have no choice but to adopt a single-blinding (outcome-assessor-blinding) approach, because sham treatment is impossible due to the characteristics of the KT method. Efforts to maintain objectivity include separating the CRC who manages the treatment schedules, the practitioner who conducts the treatments, and the assessor.

The results of this study will provide preliminary evidence on the utility and acceptability of KT for patients with grade-I and -II ankle sprains, and will serve as a basis for further research.

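### One role generates the allocation sequence, enrols and assigns, and no stated safeguard keeps the list from the person who enrols

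*Protocol article*

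**What the plan says.** The Implementation section is a single sentence: "A CRC will generate the allocation sequence, enroll participants, and assign participants to interventions". CRC stands for clinical research coordinator.

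The Participant recruitment section brings the same role into contact with candidates before consent: "Participants will be given an explanation of the study by the Clinical Research Coordinator (CRC), and will voluntarily sign a form consenting to participation".

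The Randomization section places allocation after consent and baseline measurement and uses SPSS "to assign a serial number to the 60 research volunteers and to randomly allocate 30 of them into each group". It then describes the concealment device: "The serial number codes will be inserted into opaque envelopes that will be sealed and kept in a double-locked cabinet". The envelopes are opened in front of the patient and a guardian. The section on confidentiality and data management repeats this and, like the Randomization section, does not say who fills the envelopes or holds the key.

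The Blinding section offers one measure against selection bias. It begins "To prevent risks of bias with regard to selection, performance, and attrition" and relies on involving only staff who have no conflict of interest and no prior leaning. The Discussion adds that objectivity is supported by "separating the CRC who manages the treatment schedules, the practitioner who conducts the treatments, and the assessor".

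**The concern.** Concealment means that the person who decides whether and when a candidate enters cannot know the next assignment. A sealed envelope provides this only against people who have not seen the list. Under the Implementation section, the role that produces the list is also the role that enrols.

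Three features make foreknowledge more harmful in this trial:

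- **Open treatment.** The Discussion concedes that "we have no choice but to adopt a single-blinding (outcome-assessor-blinding) approach". Participants and practitioners know the arm.
- **Self-reported primary outcome.** Pain is marked by the patient on a visual analogue line, so differences between arms in the kind of patient who enters pass straight into the endpoint.
- **Discretionary entry.** The exclusion criteria include an unsatisfactory general condition and unfitness for either therapy, neither of which has a measurable definition.

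What is at stake is the comparability of the two arms at entry. Covariate adjustment can correct for prognostic differences that were recorded, but not for those that were not.

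**Working it through.** The point rests on no figure in the plan, so the check is a side-by-side reading.

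**1. Who does what.**

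| Task | Who does it | Section |
|---|---|---|
| Explain the study to candidates | CRC | Participant recruitment |
| Generate the sequence | CRC | Implementation |
| Enrol | CRC | Implementation |
| Assign to arms | CRC | Implementation |
| Fill and number the envelopes | not named | Randomization |
| Hold the cabinet key | not named | Randomization; Confidentiality and data management |
| Judge eligibility and grade the sprain | not named | Inclusion criteria; Exclusion criteria |

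The second and third rows are the defect. This is not a detail left to a fuller document: the article states who performs these tasks.

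**2. When the list exists.** Two readings of the Randomization section are possible.

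- Each assignment is generated only after that participant's consent and baseline. Nobody could then know it in advance.
- One list of 60 is made and stored in envelopes.

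The second fits the text better. All 60 are allocated in one step, 30 to each arm, and the codes are sealed and locked away, which serves a purpose only if they exist before use. Making the list after all 60 have consented does not fit an entry criterion of a sprain within the last 7 days.

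**3. What each stated safeguard covers.**

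- *Sealed opaque envelopes in a locked cabinet:* hide assignments from staff who lack the list. They do not hide them from its maker.
- *Witnessed opening:* guards against substitution at that moment. It comes after the decision to enrol.
- *Staff without prior leanings:* an assurance about attitudes, not a concealment procedure.
- *Separation of coordinator, practitioner and assessor:* protects outcome assessment. It leaves generation and enrolment together.

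No stated safeguard withholds the list from the enroller.

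**4. Context on predictability.** Assume someone has no list but knows the fixed split, sees past assignments, and always guesses the arm with more places left. With b places per arm, the expected proportion of correct guesses is [b + (2^(2b)/C(2b,b) − 1)/2] / (2b).

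- Fixed 10:10 within a centre (Study design), b = 10: 2^20/C(20,10) = 1,048,576/184,756 = 5.675. The proportion is (10 + 4.675/2)/20 = 0.617, about 62%.
- One list of 60, b = 30: about 57%.

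A simulation gave the same values (0.617 and 0.573). Someone who made the list in advance and kept it could know every assignment. These are rates of predictability, not estimates of bias.

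**5. Sample size.** The planned 42 evaluable and 42/0.70 = 60 randomised are unaffected.

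**The case against.** The strongest reply has three parts.

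- **The coordinator is a role, and there are three centres.** Different people may do the different tasks. That is possible, but the sentence has one subject and no section says otherwise. If tasks are in fact divided, the article should say so.
- **Randomization follows consent and baseline.** If each assignment were generated at that point, foreknowledge would be impossible. The one-step allocation of 60 into stored envelopes makes this reading strained. It still stands to the extent that the article never says when the list is made.
- **The envelopes and witnessed opening do real work.** They do. They limit tampering and conceal assignments from staff who lack the list.

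A reader might also infer more than the documents support:

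- *That every assignment is foreseeable, or that the envelopes conceal nothing.* This needs the list to be made in advance and the same individual to keep or remember it. The article states neither.
- *That the coordinator judges eligibility.* The article says the coordinator enrols. It does not say who examines the ankle or decides fitness.
- *That telling grade I from grade II offers room for selection.* Both grades are eligible, so that distinction excludes nobody. Grade III is excluded, partly by numeric limits on motion loss and swelling.
- *That data handling makes it worse.* The article does say "All participant data will be recorded in Excel files by the CRC", but this has no bearing on concealment.
- *That the bias can be expressed as a share of the planned effect size of 0.906.* That would require a number of diverted patients and a prognostic difference, and the documents supply neither.

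**Conclusion.** The concern holds in this form: one role generates the sequence, enrols and assigns, and nothing stated keeps the list from the enroller. The existing measures address tampering and outcome assessment, not foreknowledge by the list's maker. Together with open treatment, a patient-marked primary outcome and two discretionary exclusions, this leaves a route to selection bias.

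The size of any bias cannot be estimated from the documents, and they do not show that selection has occurred. The conclusion assumes that the Implementation sentence means what it says, with one role holding all three tasks, and that the sequence is prepared ahead of use, as the stored envelopes imply. It should be corrected because it bears on the validity of the randomised comparison and the remedy is simple.

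**What to change.** Revise the Randomization and Implementation sections to state that:

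1. A person with no participant contact, for example a statistician, generates the sequence before the enrolment it governs.
2. That person prepares sequentially numbered, sealed, opaque envelopes and withholds the list from the sites.
3. The coordinator enrols the participant, completes baseline, writes the participant ID and date on the next envelope, and only then opens it.

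**Cost.** Preparing the list and envelopes is a one-off task with no extra visits and no change in sample size. Under Quality assurance, a protocol revision also needs approval from the Ministry of Food and Drug Safety and the three hospital IRBs.

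**Limits.** Trial status describes the study as ongoing, so the change can protect only allocations not yet made. For earlier ones, the sponsor should document who made and held the list and report this as a limitation. Withholding the list does not remove the guessing that a fixed split per centre allows, but it does remove direct knowledge of the sequence.

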### Blinding

During the course of this clinical trial, the assessor will not come into contact with any of the participants except at the time of assessment. Furthermore, under no circumstances will unblinding be permitted. To prevent risks of bias with regard to selection, performance, and attrition caused by non-blinding of participants and practitioners, only individuals without conflicts of interest or preconceived positions will be involved in this study. All practitioners will receive training in clinical trials before participation in this study.

### Intervention

After providing informed consent and completing a baseline evaluation, participants will be randomly assigned to the acupuncture and AcuKT groups. The acupuncture group will receive acupuncture treatment once per day, 5 days per week (excluding Saturday and Sunday) for 1 week. The AcuKT group will receive acupuncture treatment and the ankle meridian tendino-musculature and figure-of-eight shape form of KT treatment once per day, 5 days per week (excluding Saturday and Sunday) for 1 week. The acupuncture and KT treatment will be performed by Korean medicine physicians with 6 years of formal university training in Korean medicine, a licence to administer the treatments, and at least 2 years of clinical experience. They will be trained together and use the same techniques to ensure strict adherence to the study protocol.

All participants will receive acupuncture at ST36, ST41, BL60, BL62, KI3, KI6, GB39, and GB40 acupuncture points on the affected side [20]. Only sterile, stainless, disposable acupuncture needles (size 0.25 × 30 mm; Dong Bang Acupuncture, Inc., Boryeong, Republic of Korea; product no. A84010.02) with guide tubes will be used. The depth of insertion will be 10 to 20 mm, depending on the location of the needle [21]. After insertion, needles will be left in position for 15 min in every session. Manual stimulation and electroacupuncture will not be applied (Table 1).

**Table 1 Tab1:** Revised standards for reporting intervention in clinical trials of acupuncture (STRICTA)

	Item criteria	Description
1.Acupuncture rationale	1a) Style of acupuncture	Korean Medicine Therapy
	1b) Reasoning for treatment provided – based on historical context, literature sources, and/or consensus methods, with references where appropriate	1. Discussion among four physicians that practice Korean medicine (consensus)2. Textbook of acupuncture and moxibustion medicine3. Relevant articles [20]Selection of treatment regions based on textbooks, related papers, and expert discussions
	1c) Extent to which treatment varied	Standardized treatment
2. Details of needling	2a) Number of needle insertions per subject per session (mean and range where relevant)	8
	2b) Names (or location if no standard name) of points used (uni/bilateral)	ST36, ST41, BL60, BL62, KI3, KI6, GB39, GB40
	2c) Depth of insertion, based on a specified unit of measurement or on a particular tissue level	The depth of insertion is 10 to 20 mm, depending on the location of the needle [21]
	2d) Responses sought	No *de qi* or muscle twitching – only sensation due to needle insertion
	2e) Needle stimulation	None
	2f) Needle retention time	15 min per session
	2 g) Needle type	sterile, stainless, disposable acupuncture needles (size 0.25 × 30mm; Dong Bang Acupuncture, Inc., Boryeong, Republic of Korea; Product no: A 84010.02)
3. Treatment regimen	3a) Number of treatment sessions	5
	3b) Frequency and duration of treatment sessions	5 times/week for 1 weeks, 15 min per session
4. Other treatment components	4a) Details of other interventions administered to the acupuncture group	None
	4b) Setting and context of treatment – including instructions to practitioners – as well as information and explanations given to patients	Practitioner-patient conversation about the context of the treatment, life habits, and daily life management
5. Practitioner background	5a) Description of participating acupuncturists	Korean medicine physician with the following qualifications: 6 years of formal university training in Korean medicine, a licence, and at least 2 years of clinical experience
6. Control or comparator interventions	6a) Rationale for the control or comparator in the context of the research question, with sources that justify the choice	Korea Institute of Oriental Medicine. Ankle sprain Korean Medicine Clinical Practice Guideline. Seoul: Elsevier Korea, L.C.C. 2015;163–7.
	6b) Precise description of the control or comparator; details for items 1–3 above with the use of sham acupuncture or any other type of acupuncture-like control	Acupuncture combined with Kinesiotape (AcuKT) group will receive the ankle meridian tendino-musculature and figure-of-eight shape form of KT treatment after acupuncture treatment by the same practitioner. The KT treatment method will be conducted as follows: first, an I-shaped tape will be applied from ST42 to ST36 over the tibialis anterior muscle. Second, an I-shaped tape will be applied from GB42 to GB34 over peroneus longus and brevis muscles. Third, an I-shaped tape will be applied from abductor digiti minimi muscle and wrap around the ankle like a figure-of-eight shape to the abductor hallucis muscle covering both medial and lateral malleoli

The participants randomly assigned to the AcuKT group will receive the ankle meridian tendino-musculature and figure-of-eight shape form of KT treatment after acupuncture treatment by the same practitioner. The KT treatment method will be conducted as follows: first, an I-shaped tape will be applied from ST42 to ST36 over the tibialis anterior muscle (Fig. 3 ① to ③). Second, an I-shaped tape will be applied from GB42 to GB34 over the peroneus longus and brevis muscles (Fig. 3 ④ to ⑥). Third, an I-shaped tape will be applied from the abductor digiti minimi muscle and wrapped around the ankle in a figure-of-eight shape to the abductor hallucis muscle, covering both the medial and lateral malleoli (Fig. 3 ⑦ to ⑨) [22]. NK-50 KT will be used (width 50 mm, thickness 0.5 mm; Nitto Denko Medical MFG. Co., Ltd., Miyagi, Japan; Product no. B07090.02). The tape will be laid on the skin without being stretched, to prevent skin problems. The KT treatment will be applied daily after removal of the tape applied the previous day, even in cases in which the patient does not complain of itchiness [23]. During the clinical trial period, all participants will be allowed to use routine management, existing medications (e.g*.*, for hypertension, diabetes, hyperlipidemia, or improvement of brain function), and medications to maintain and improve health status. However, patients will not be permitted to engage in treatments to improve ankle-sprain symptoms, other than the therapies administered as part of this study. All medical devices will be inspected by investigators, including acupuncture needles and KT. Investigators will record the results of check-ups in the management register.

**Fig. 3 Fig3:**
[figure not shown]
Application of Kinesiotape

### Outcome measurements

VAS, FAOS, and edema measurements will be performed at baseline (before intervention), 5 days after the first intervention (i.e., at the end of the intervention), and 4 weeks after the completion of intervention. EQ-5D-5 L measurements will be conducted at baseline, 5 days after the first intervention, 4 weeks after the completion of intervention, and 26 weeks after the completion of intervention. Numbers of recurrent ankle sprains will be assessed at 4, 8, 12, and 26 weeks after the completion of intervention.

#### Primary outcome

Given that the objective of this study is to investigate the efficacy of KT on pain reduction in patients with ALAS, the primary outcome assessed will be changes in pain as determined via VAS, which is commonly used in clinical trials and other studies to determine primary outcomes. The VAS that will be used in this study is a 10-cm-long straight line marked at each end with labels that anchor the scale [24]. Patients will be asked to place a mark on the line at a point representing the severity of their pain, where the anchors are “no pain” and “pain as bad as it could be.” Scores are recorded in millimeters, thus yielding a total score range of 0–100 mm. The VAS is often treated as an interval-level scale (with equality between intervals) and subjected to arithmetic operations (e.g., calculation of change scores) and parametric statistics [25].

#### Secondary outcomes

The secondary outcomes assessed will be changes in FAOS, edema, EQ-5D-5 L, and the number of recurrent ankle sprains. The FAOS is a self-administered questionnaire specific for feet and ankles, designed to assess week-to-week changes in symptoms and function after foot and ankle injuries. It consists of five subscales, pain, other symptoms, activities of daily living, functioning in sport and recreation, and foot- and ankle-related quality of life (QoL). The last week is taken into consideration when the answering options are given (% Likert boxes), and each question is scored from 0 to 4. A normalized score (in which100 indicates no symptoms and 0 indicates extreme symptoms) is calculated for each subscale [26].

Edema will be measured in cm via the figure-of-eight method. The measuring tape will be applied such that the following landmarks will be crossed in a figure-of-eight fashion: (1) navicular tuberosity; (2) distal tip of the lateral malleolus; (3) distal tip of the medial malleolus; and (4) base of the fifth metatarsal. The resulting measurement will be compared with a corresponding measurement derived from the uninjured ankle [27].

The European Quality of Life Five Dimension Scale (EQ-5D) is a generic instrument for assessing health-related QoL. It is based on a descriptive system that defines health in terms of five dimensions, mobility, self-care, usual activities, pain/discomfort, and anxiety/depression. Each dimension has three response categories corresponding to no problems, some problems, and extreme problems. The EQ-5D-5 L, which will be used in this study, is a new version of the EQ-5D that includes five levels of severity in each of the existing five EQ-5D dimensions [28].

Ankle sprain recurrence is defined as an ankle sprain occurring as a result of sports participation or other daily activities, and which causes one or more of the following: (1) the subject has to stop the sports activity; (2) the subject cannot fully participate in the next planned sports activity; (3) the subject cannot go to work/school the next day; or (4) the subject requires medical attention (ranging from onsite care administered by a GP to personal care administered by a sports physician) [29].

